# RADAR – A randomised, multi-centre, prospective study comparing best medical treatment versus best medical treatment plus renal artery stenting in patients with haemodynamically relevant atherosclerotic renal artery stenosis

**DOI:** 10.1186/1745-6215-10-60

**Published:** 2009-07-27

## Abstract

**Background:**

Prospective, international, multi-centre, randomised (1:1) trial to evaluate the clinical impact of percutaneous transluminal renal artery stenting (PTRAS) on the impaired renal function measured by the estimated glomerular filtration rate (eGFR) in patients with haemodynamically significant atherosclerotic renal artery stenosis.

**Methods:**

Patients will be randomised to receive either PTRAS using the Dynamic Renal Stent system plus best medical treatment or best medical treatment. Renal stenting will be performed under angiographic imaging. For patients randomised to best medical treatment the degree of stenosis measured by renal duplex sonography (RDS) will be confirmed by MR angio or multi-slice CT where possible. Best medical treatment will be initiated at randomisation or post procedure (for PTRAS arm only), and adjusted as needed at all visits. Best medical treatment is defined as optimal drug therapy for control of the major risk factors (blood pressure ≤ 125/80 mmHg, LDL cholesterol ≤ 100 mg/dL, HbA1c ≤ 6.5%). Data recordings include serum creatinine values, eGFR, brain natriuretic peptide, patients' medical history and concomitant medication, clinical events, quality of life questionnaire (SF-12v2™), 24 hour ambulatory blood pressure measurement, renal artery duplex ultrasound and echocardiography. Follow-up intervals are at 2, 6, 12 and 36 months following randomisation.

The primary endpoint is the difference between treatments in change of eGFR over 12 months. Major secondary endpoints are technical success, change of renal function based on the eGFR slope change between pre-treatment and post-treatment (i.e. improvement, stabilisation, failure), clinical events overall such as renal or cardiac death, stroke, myocardial infarction, hospitalisation for congestive heart failure, progressive renal insufficiency (i.e. need for dialysis), need of target vessel revascularisation or target lesion revascularisation, change in average systolic and diastolic blood pressure, change in left ventricular mass index calculated from echocardiography, difference in the size of kidney (pole to pole length) measured by renal duplex sonography, total number, drug name, drug class, daily dose, regimen and Defined Daily Dose (DDD), of anti-hypertensive drugs, and change in New York Heart Association (NYHA) classification. Approximately 30 centres in Europe and South America will enrol patients. Duration of enrolment is expected to be 12 months resulting in study duration of 48 months.

**Trial registration:**

**Trial registration number**: NCT00640406

## Background

Renal artery stenosis (RAS) usually refers to a disease of the large extra-renal arterial vessels and most frequently is caused by atherosclerotic obstructions. Arterial hypertension, progressive renal failure and flash pulmonary oedema are clinical manifestations of RAS requiring intervention and treatment and may be resolved by revascularisation therapy. In the past, RAS was under recognised, under diagnosed and under treated. With improved non-invasive imaging techniques such as magnetic resonance imaging angiography, computed tomography angiography and high resolution renal duplex sonography, the diagnosis is currently more frequently established.

Atherosclerosis accounts for approximately 90% of cases with RAS and most commonly involves the origin and the proximal third of the main renal artery. In fact, ostial RAS can be considered as a combined disease of the aorta and the renal artery, rather than an isolated problem of the renal arteries. The prevalence of atherosclerotic RAS increases with age, male gender, traditional cardiovascular risk factors (hypertension, diabetes, smoking, disease, in particular aorto-iliac occlusive disease) [1]. However, the true prevalence of atherosclerotic RAS in unselected patients is unknown. In hypertensive patients, a significant RAS is observed in below 5% [2], whereas a prevalence of up to 12% has been reported in patients with coronary artery disease undergoing cardiac catheterisation [3] and up to 40% in patients with peripheral artery disease (PAD). Undoubtedly, atherosclerotic RAS is a progressive disease [4], as more than half of the patients exhibit an increasing degree of stenosis within five years after diagnosis [5], and one out of five patients with a critical stenosis suffers renal atrophy and renal failure during this period [1].

RAS may be treated conservatively by so called best medical treatment, surgically, or by endovascular interventions using balloon angioplasty and stenting. Applying endovascular therapy, there is general agreement that ostial lesions should be stented as it improves primary patency rates and reduces the burden of reintervention [6-11].

This study (RADAR) is designed to compare the best medical treatment versus the best medical treatment plus renal artery stenting with the Dynamic Renal stent (BIOTRONIK, Bülach, Switzerland) in patients with haemodynamically significant atherosclerotic renal artery stenosis. The key inclusion criterion is the proof of significance of RAS by duplex ultrasound in terms of significantly reduced intra-renal resistance index and extended acceleration time at the affected side. Both parameters correlate closely with an angiographic diameter reduction of at least 70%. This selection criterion should exclude patients without haemodynamically relevant RAS from study entry.

## Methods

### Study design

RADAR is designed as randomised, multi-centre, prospective study. Patients with haemodynamically relevant atherosclerotic RAS matching the inclusion and passing all exclusion criteria will be randomised to receive best medical treatment or best medical treatment plus renal artery stenting. Best medical treatment is defined as optimal drug therapy for control of hypertension (blood pressure ≤ 125/80 mmHg), of hypercholesterolemia (LDL ≤ 100 mg/dL), and of diabetes (HbA1c ≤ 6.5%).

The objective of this study is to evaluate the clinical impact of percutaneous transluminal renal artery stenting (PTRAS) on the impaired renal function measured by the estimated Glomerular Filtration Rate (eGFR) in patients with haemodynamically relevant atherosclerotic RAS. Furthermore the effect of PTRAS on renal function, hypertension and quality of life in comparison to medical treatment will be evaluated. Safety and efficacy of both treatments are further endpoints of this study. Figure 1 shows the study profile.

**Figure 1 F1:**
[figure not shown]
**Study profile**.

Serum Creatinine (SCr) values and eGFR will be assessed from patient's medical files after obtaining informed consent, and a blood sample for determination of the baseline value will be obtained. At time of randomisation the patient's medical history and concomitant medication, clinical events and quality of life will be recorded. A 24 hour ambulatory blood pressure measurement will be obtained. Renal stenting will be performed under angiography imaging. For patients randomised to best medical treatment the degree of stenosis measured by renal duplex sonography will be confirmed by MR angiogram or multi-slice CT where possible. Best medical treatment will be initiated at randomisation or post procedurally (for PTRAS arm only), and adjusted as needed at all visits. For all patients renal duplex sonography will be performed at baseline, post procedure (for PTRAS arm only), and at 6 and 12 months follow up. Clinical events will be obtained at baseline and during all visits including a telephone follow up 3 years after randomisation. Twenty four hour ambulatory blood pressure measurement and blood sampling for eGFR determination will be done at baseline, post procedure (for PTRAS arm only), and after 2, 6 and 12 months. Adverse events and concomitant medication will be recorded up to 12 months after randomisation. At baseline, 6 and 12 months patients' quality of life will be assessed using a validated general health quality instrument (SF-12v2™). For further assessments see flow chart and table of events. Patients randomised to the 'no revascularisation'-group and presenting with a severe increase in serum creatinine concentration indicating the need of renal replacement therapy, or recurrent flash pulmonary oedema despite existing multidrug therapy (5 drugs), may receive a Dynamic Renal stent.

Only patients who have given written informed consent in accordance with the applicable regulations, the Declaration of Helsinki, GCP and ISO 14155 will be enrolled in the trial. The trial is conducted in compliance with the Declaration of Helsinki. The trial was approved by the central ethics commission "Ethik-Komission der Albert-Ludwigs-Universität Freiburg", Freiburg, Germany

### Endpoints

*Primary Endpoint*: The primary endpoint is the difference between treatments in change of eGFR over 12 months.

*Secondary Endpoints*: Secondary endpoints are defined as:

• Change in eGFR at 2, 6 and 12 months.

• Difference between treatments in change of eGFR over 2 and 6 months.

• Difference in eGFR slope between pre-treatment and post treatment time points at 2, 6 and 12 months.

• Change of renal function based on the eGFR slope change between pre-treatment and post-treatment at 2, 6 and 12 months (i.e. improvement, stabilisation, failure).

• Ratio of average Resistance Index (RI) at baseline, 6 and 12 months. Intra-renal Resistance Index is defined and calculated by the following formula: Intra-renal RI = (Peak Systolic Velocity-End Diastolic Velocity)/Peak Systolic Velocity.

• Degree of restenosis at 6 and 12 months.

• Clinical events overall: renal or cardiac death, stroke, myocardial infarction, hospitalisation for congestive heart failure, progressive renal insufficiency (i.e. need for dialysis), need for permanent renal replacement therapy, and need of target vessel revascularisation (TVR) or target lesion revascularisation (TLR) at 2, 6 and 12 months, and 3 years.

• Clinical events renal: renal death according to ICD 10, progressive renal insufficiency (i.e. need for dialysis), need for permanent renal replacement therapy, and need of TVR or TLR at 2, 6 and 12 months, and 3 years.

• MACCE: cardiac death, stroke, myocardial infarction, hospitalisation for congestive heart failure at 2, 6 and 12 months, and 3 years.

• Technical success, defined as successful access and deployment of the device with appropriate lesion coverage, stent positioning and patency determined by angiography.

• Acute procedural success, defined as residual percent diameter stenosis <30% by quantitative computerised angiography.

• Procedural success, defined as successful lesion crossing and stent positioning without the occurrence of a serious adverse event up to the moment the introducer sheath is removed,

• Average systolic and diastolic blood pressure (i.e. ambulatory 24 h-BP) at baseline, post procedure, 2, 6 and 12 months.

• Change in average systolic and diastolic blood pressure (i.e. ambulatory 24 h-blood pressure monitoring) at 2, 6 and 12 months.

• Left ventricular mass index (LVMI) calculated from echocardiography or cardiac magnet resonance imaging at baseline and 12 months. The LVMI [g/m^2^] is defined as left ventricular mass divided by body surface area [m^2^]. Left ventricular mass is calculated by using the method described by Devereux and Reichek [21], or as supplied by the manufacturer of the echo device.

• Difference in the size of kidney (pole to pole length) at baseline, 6 and 12 months measured by renal duplex sonography.

• Total number, drug name, drug class, daily dose, regimen and Defined Daily Dose (DDD), of anti-hypertensive drugs at baseline, 2, 6 and 12 months.

• Change in anti-hypertensive therapy at 2, 6 and 12 months.

• Classification of heart failure according to the New York Heart Association (NYHA) at baseline, 2, 6 and 12 months.

• Change in NYHA classification of heart failure at 2, 6 and 12 months.

• Quality of life at baseline, 6 and 12 months (i.e. SF-12v2™).

• Change in quality of life at 6 and 12 months.

• Patient survival

• Laboratory parameters at baseline, 2, 6 and 12 months (blood), or baseline and 12 months (urine).

• Adverse events.

### Patient population

Three hundred patients will be included to yield at least 250 patients with valid primary endpoint. Patients will be enrolled in approximately 30 centres in Europe and South America. Patient recruitment should be finished within 1 year following the initiation of the last study centre. Study duration would be 4 years.

Selection of participants for this study will be documented on the screening log. The patients being eligible for this study must meet ALL of the following inclusion and NONE of the exclusion criteria.

#### Inclusion Criteria

1. Age ≥ 18 years,

2. Informed consent signed by patient (and/or legal guardian),

3. Haemodynamically relevant de novo unilateral or bilateral RAS (≥ 70%). In case of unilateral disease, haemodynamically relevant RAS is defined by an intra-renal Resistance Index difference dRI > 0.05 (RI values comparison between the two individual kidneys). The lower RI value indicates the kidney with the stenosed artery. In presence of bilateral symmetric disease, RAS ≥ 70% is defined by an acceleration time more than 0.07 sec.

4. Estimated GFR > 10 ml/min calculated using the abbreviated Modification of Diet in Renal Disease (MDRD) Study equation,

5. Patients presenting mild, moderate or severe hypertension (defined according to the WHO guidelines) and/or renal dysfunction,

6. Target lesion must be completely coverable by one study stent (total target lesion length estimated to be less than 19 mm),

7. Target lesion accessible to direct stenting or, after pre-dilation, is likely to sufficiently benefit from stenting (at the discretion of the investigator),

8. Renal reference vessel diameter (RVD) of ≥ 4.0 mm and < 7.0 mm based on visual estimation,

9. Willingness to comply with all the specified follow-up evaluations.

#### Exclusion Criteria

Target indication and treatment:

1. Estimated GFR ≤ 10 ml/min,

2. Renal atrophy or kidney length < 7 cm (referring to kidney with target lesion),

3. Patient not eligible for PTRA,

4. Patient not eligible for stenting,

5. Target lesion occlusion,

6. Target lesion and/or target vessel proximal to the target lesion is severely calcified,

7. Treatment of branch lesion required,

8. Fresh thrombus or embolic lesion,

##### Medical history

9. Need for embolic protection in previous or planned PTRAS,

10. Clotting disorders,

11. INR < 2.5 in patients using warfarin treatment,

12. Patient presents fibromuscular dysplasia,

13. Prior revascularisation of target lesion,

14. History of target vessel revascularisation within the last 6 months,

15. Angiographic restenosis of any segment of the target vessel that has undergone prior percutaneous intervention,

16. Any thrombolytic therapy procedure within 72 hours prior to planned study procedure

17. Active peptic ulcer or gastro-intestinal bleeding,

18. Active inflammation of the kidney interfering with diagnosis and treatment of RAS (e.g. glomerulonephritis, aortitis, vasculitis),

19. Radiation damage of the kidney,

20. Renal disease associated with aortic aneurysm i.e. diameter of the aorta > 40 mm,

21. Chronic renal replacement therapy,

22. Life expectancy < 1 year,

23. Co-morbid conditions limiting participation and follow-up,

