#### Device sizes

The Dynamic Renal stent system is available in 16 different variants. The stent is available in lengths of 12 and 19 mm. It is pre-mounted on a delivery system which has nominal balloon diameters of 4.5, 5.0, 6.0 and 7.0 mm and usable lengths of 80 cm and 140 cm respectively that allow a femoral or brachial/radial access route.

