## Abbreviations

": Inch; 24h-BP: blood pressure obtained during 24 hour continuous assessment; ADE: Adverse device effect; AE: Adverse event; ASA: acetylic salicylic acid; a-SiC:H: amorphous hydrogen-rich silicon carbide; BMT: Best Medical Treatment; BP: blood pressure; CEC: Clinical Event Committee; cm: centimetre; CoCr: Cobalt chromium; CRF: Case report form; CT: Computerized tomography; DDD: defined daily dose according to WHO drug dictionary; dL: decilitre; ΔRI: difference in RI between the two kidneys; DSMB: Data Safety Monitoring Board; ECHO: Echocardiogram; eGFR: estimated GFR; g: gram; F: French; g/m^2^: gram per square meter; GFR: glomerular filtration rate (in this study the eGFR will be used); HbA1c: hemoglobin A1c; ICD: International Classification of Disease; i.e.: *id est *(that is); IEC: Independent Ethic Committee; INR: International normalized ratio; IRB: Institutional Review Board; ITT: intention to treat; LDL: low density lipoprotein; LVMI: left ventricular mass index; m^2^: square meter; MACCE: Major Adverse Cardiac and Cerebral Events; MDRD: Modification of diet in Renal Disease (study); mg: milligram; min: minute; ml: millilitre; mm: millimetre; mmHg: Milliliters of mercury; MR: Magnetic resonance; NYHA: New York heart association; PAD: peripheral artery disease; PTRA: percutaneous transluminal renal angioplasty; PTRAS: percutaneous transluminal renal arterial stenting; RAS: renal artery stenosis; RCT: Randomised controlled trial; RDS: renal duplex sonography; RI: resistance index; RVD: reference vessel diameter; SADE: Serious adverse device effect; SAE: Serious adverse event; SCr: serum creatinine; sec: Second; TLR: target lesion revascularization; TVR: target vessel revascularization; U: Unit; WHO: World Health Organization.

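### Exclusion 11 appears to have its INR inequality reversed: it bars warfarin patients below 2.5 and leaves those at or above 2.5 without a limit before arterial stenting

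*Protocol article*

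**What the plan says.** The Patient population section sets the rule for applying the lists: eligible patients "must meet ALL of the following inclusion and NONE of the exclusion criteria". Under Exclusion Criteria, in the Medical history block, item 11 is "INR < 2.5 in patients using warfarin treatment".

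The same block contains three other items on coagulation or bleeding:

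- item 10: "Clotting disorders"
- item 16: "Any thrombolytic therapy procedure within 72 hours prior to planned study procedure"
- item 17: "Active peptic ulcer or gastro-intestinal bleeding"

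The procedure is arterial. The Device sizes section says the delivery-system lengths "allow a femoral or brachial/radial access route". The only other mention of INR in the article is its entry in the Abbreviations list, "INR: International normalized ratio".

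**The concern.** An INR criterion applied before an arterial puncture would be expected to keep out patients who are too heavily anticoagulated. As printed, item 11 removes the less anticoagulated warfarin patients and places no bar on the more anticoagulated ones.

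Two things are at stake. Warfarin patients with a lower INR, who would be the safer candidates for the procedure, are refused entry to either arm. Those with a high INR are left to the investigator's judgement, with no numerical limit. Neither affects the comparison of eGFR change between arms or the power of the trial; this concerns who may enter and how safely they are treated.

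**Working it through.** No figure in the plan needs reproducing. The check is a literal reading of the rule, followed by three tests of whether that reading could be intended.

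**1. The rule as printed and reversed.** The inputs are the cut-off of 2.5 from item 11 and the rule that meeting any exclusion bars entry. The INR values are illustrative.

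| INR on warfarin | As printed (exclude if < 2.5) | Reversed (exclude if > 2.5) |
|---|---|---|
| 2.0 | 2.0 < 2.5 is true: excluded | 2.0 > 2.5 is false: not barred |
| 4.0 | 4.0 < 2.5 is false: not barred | 4.0 > 2.5 is true: excluded |

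The two forms give opposite results for both patients.

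**2. Consistency with neighbouring items.** Items 16 and 17 exclude patients at raised risk of bleeding, and item 10 excludes disordered clotting. Exclusion 27 bars known intolerance to aspirin, heparin and thienopyridines, which implies that antithrombotic drugs are expected around the procedure in addition to any warfarin effect. The reversed form of item 11 fits this group; the printed form works against it.

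**3. Support elsewhere for a minimum INR.** There is none. Apart from item 11, INR appears only as an abbreviation, so the number of upper INR limits stated in the article is 0, and no rationale is given for a floor.

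**4. Could the PDF reading have changed the sign?** Counting inequality symbols in the eligibility lists:

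- inclusion criteria: ≥ 18 years, ≥ 70%, > 0.05, ≥ 70%, > 10 ml/min, ≥ 4.0 mm, < 7.0 mm, which is 7
- exclusion criteria: ≤ 10 ml/min, < 7 cm, INR < 2.5, > 40 mm, < 1 year, which is 5

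The total is 7 + 5 = 12. Eleven point in a sensible direction, and item 11 is the only one that does not. Some symbols in the Sample Size Calculation section are damaged (the not-equal sign and some subscripts), but the plain < and > signs in the same hypothesis statement are intact. A clean swap at this one place is therefore unlikely to come from the text extraction.

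**The case against.** The strongest reply is that the article never states the purpose of item 11. The same lists also contain items pointing to thrombo-embolic concern: fresh thrombus or embolic lesions (item 8) and need for embolic protection (item 9). A floor against inadequate anticoagulation is therefore not strictly ruled out. This stands as a limit on certainty: the document supports an apparent reversal, not a proven one. It does not rescue the printed rule, because nothing in the text asks for a minimum INR and an arterial procedure is an unlikely setting for one. If the line was meant as a condition for entry, it is in the wrong list and the correction is the same in substance.

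A second reply is that "Patient not eligible for PTRA" (item 3) and its companion on stenting (item 4) let the investigator refuse an over-anticoagulated patient. That is true, and it reduces the safety consequence, as does the fact that half of those randomised are not assigned to stenting. But those items set no INR value and cannot readmit the low-INR patients whom item 11 bars.

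A third reply is that a condensed article may leave peri-procedural anticoagulation to the full protocol. That would answer a complaint about missing detail. Here the article states an explicit eligibility rule, and the lack of a ceiling follows directly from the direction of its sign.

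Finally, if the sign is wrong, the value 2.5 may be wrong too. That is a fair caution and is carried into the fix.

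**Conclusion.** The concern holds: exclusion 11 is wrong as written. Followed literally, it bars warfarin patients below an INR of 2.5 and does not bar any at or above it. Confidence that the sign is reversed is medium, because the intended direction is inferred from the arterial procedure and the neighbouring bleeding exclusions.

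The consequence is confined to eligibility and procedural safety. The number of patients concerned cannot be derived without the proportion on warfarin. It is not shown that any over-anticoagulated patient would in fact be enrolled. This should be corrected because it is an operative selection rule and the correction costs almost nothing.

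**What to change.** Reverse the inequality, so that exclusion 11 excludes warfarin patients with INR > 2.5. Before issuing it, the sponsor should check both direction and cut-off against the full protocol, since the article gives no independent support for 2.5 as an upper limit. It would help to state when the INR is measured relative to the procedure. If the protocol held by sites has the same wording, send them the corrected criterion.

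The cost is one sign in one criterion and, if needed, one notice to sites. The sample size and the analysis are unchanged.
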